*Randomized Controlled Multicenter Study* ● Signed and dated informed consent form. ● 18 years of age and older. ● Diagnosis of unresectable Stage 3 pancreatic adenocarcinoma cancer cytologically or pathologically confirmed per American Joint Committee on Cancer (AJCC) staging criteria. ● Tumor evaluated as Stage 3 according to National Comprehensive Cancer Network (NCCN) guidelines, based on radiographic imaging or exploratory surgery. ● Maximum axial and anterior to posterior tumor dimension of ≤3.5 cm, after receiving three months of treatment with the mFOLFIRINOX regimen. ● Has received 3 months of treatment with the mFOLFIRINOX regimen. ● Has an Eastern Cooperative Oncology Group (ECOG) performance status of 0 or 1. ● Has an American Society of Anesthesiologists (ASA) classification of physical health status of 1, 2, 3 or 4.	*Multicenter Registry* ● Signed and dated informed consent form ● 18 years of age and older ● Diagnosis of Stage 3 PC cytologically or pathologically confirmed per American Joint Committee on Cancer (AJCC) staging criteria. ● Tumor evaluated as Stage 3 according to National Comprehensive Cancer Network (NCCN) guidelines, based on radiographic imaging or exploratory surgery ● Maximum axial and anterior to posterior tumor dimension of ≤3.5 cm after standard of care. ● Has received 3 months of standard of care per each participating institution’s guidelines ● Has an Eastern Cooperative Oncology Group (ECOG) performance status of 0 or 1. ● Has an American Society of Anesthesiologists (ASA) classification of physical health status of 1, 2, 3 or 4. ● Are at an IRE site and are deemed eligible for IRE and receive ablation using the NanoKnife System. ● Shows no evidence of disease progression based on NCCN guidelines after completing 3 months of standard of care.
Key Exclusion Criteria	

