#### Study endpoints and assessments

The primary efficacy endpoint for both the RCT and the registry study will be OS defined as the time (in months) from randomization or enrollment in the registry to the date of death for any reason. Co-primary safety endpoints include time (in months) from randomization or enrollment in the registry to death or new onset of Grade 4 AE, and the development of high-grade complications defined as any AE or SAE with a CTCAE v5.0 grade of 3 or higher.

Secondary endpoints for both studies include a) PFS defined as the time (in months) from randomization or enrollment in the registry to the date of first observed disease progression (per clinical and radiologic criteria), or death from any cause, if death occurs without documented disease progression, b) procedure-related pain in subjects in the IRE arm, as measured by the Brief Pain Inventory (BPI-SHORT FORM) on the day of the procedure and post-procedure days 1, 7, 14 and 30, c) cancer-related pain assessed in the control and IRE arms using the BPI-SHORT FORM at baseline, 3 months, 6 months and at 6-month intervals thereafter, and d) QOL assessed in the control and IRE arms using the EQ-5D questionnaire at baseline, 3 months, 6 months and then at 6-month intervals for the duration of the study.

The registry study will also assess several exploratory endpoints including chemotherapy-free days (after 3 months of SOC), the need for opioids for cancer-related pain, OS from date of pancreatic cancer diagnosis, PFS from date of enrollment, and identification of risk factors and biomarkers associated with outcomes. Additional QOL exploratory endpoints which will be collected include rates of avoidable events associate with chemotherapy in the IRE arm during chemotherapy free days compared to the control arm, unplanned readmissions within 30 days following discharge, and in-hospital mortality.

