Subjects who do not have disease progression and have not died, will be censored at the date of last tumor assessment. Subjects with a single missing radiologic or clinical assessment immediately prior to a visit with documented disease progression (or death) will be analyzed as a PFS event at the time of the clinical or radiologic assessment that shows progression. Subjects with two or more consecutive missing radiologic or clinical assessments immediately prior to an assessment without documented progression (or death) will be censored at the date of last assessment when the subject was documented as progression-free prior to the first of the two or more missing assessments. PFS will be analyzed using similar statistical methods as that for the OS endpoint.

Pain Severity Scores and average Pain Interference Score will be derived for each subject from BPI-SHORT FORM questionnaire. QOL measures will be derived for each subject from the EQ-5D questionnaire, including the EQ Visual Analogue Scale (VAS) and EQ-5D summary index. Both absolute change and percent change from baseline will be analyzed by treatment arm and by study visit for all of the above.

For the primary safety endpoints, a log-rank test will be used to compare the time (in months) from randomization to death or new onset of Grade 4 AEs for the two treatment arms, with data censored at the time of loss to follow up or study discontinuation. The number and proportion of subjects with a high-grade complication defined as any AEs or SAEs with a CTCAEv5.0 grade of 3 or higher will be summarized by treatment arm and CTCAE grade.

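### Percent change from baseline is fixed as an analysis variable for pain and quality of life, although it has no value at a zero baseline and misleads near or below zero

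*Protocol article*

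**What the plan says.** In the protocol article, under Statistical analysis, Randomized controlled trial, the patient-reported measures are defined first. For pain: "Pain Severity Scores and average Pain Interference Score will be derived for each subject from BPI-SHORT FORM questionnaire". For quality of life, the EQ-5D measures are named as "including the EQ Visual Analogue Scale (VAS) and EQ-5D summary index". The analysis follows in one sentence, which applies to every measure just named: "Both absolute change and percent change from baseline will be analyzed by treatment arm and by study visit". It covers four measures: BPI severity, BPI interference, EQ VAS and the EQ-5D index. It gives neither form of change precedence, gives no rule for a zero baseline, and names no model, test or covariate.

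Under Study endpoints and assessments, both instruments are collected at baseline in both arms: "cancer-related pain assessed in the control and IRE arms using the BPI-SHORT FORM at baseline, 3 months, 6 months and at 6-month intervals thereafter", and "QOL assessed in the control and IRE arms using the EQ-5D questionnaire at baseline, 3 months, 6 months and then at 6-month intervals".

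The key inclusion criteria for the RCT (Table 1) set no minimum pain score. They do require good performance status: "Has an Eastern Cooperative Oncology Group (ECOG) performance status of 0 or 1".

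**The concern.** Percent change divides by the baseline score. A patient who reports no pain at baseline has a score of 0, so the quantity does not exist for that patient. An EQ-5D index of 0 gives the same problem, and a negative index reverses the sign. Small positive baselines produce very large percentages that drive the mean.

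Comparing cancer-related pain and quality of life between arms is a stated secondary objective, and the Discussion makes less pain and better quality of life a goal of the study. Under the percent-change analysis, the patients in whom new pain would be most visible are absent. Because percent and absolute change have equal standing, the report could also contain two analyses of the same data that disagree, with nothing to say which one counts.

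**Working it through.** **Is there a figure to reproduce?** No. The article gives no sample size, power, standard deviation or effect size for pain or quality of life. Every size below rests on assumptions.

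**Step 1. Algebra of percent change.** Percent change = 100 × (follow-up − baseline) / baseline.

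- Baseline 0: division by zero, no value.
- Negative baseline (illustration: index from −0.1 to +0.1): 100 × 0.2 / (−0.1) = −200%. An improvement is scored as a large worsening.
- Unequal scoring of one point: 1 to 2 gives 100 × 1/1 = +100%; 8 to 9 gives 100 × 1/8 = +12.5%.

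The article does not print the score ranges. I take it as a property of the instruments that no pain scores 0 and that the index can reach zero or below. I make no such case for the EQ VAS.

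**Step 2. Who is affected.** The listed entry criteria do not require pain, and patients must be ECOG 0 or 1 without progression after three months of induction. Zero baselines are therefore possible. Their share is not given.

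**Step 3. Simulation of the three candidate analyses.** Assumptions: 222 patients per arm (the ITT number in the sample size section), all observed; a 0 to 10 score in steps of 0.25, from a normal variable cut off at 0 and 10; a true difference of 0.6 points before cut-off; two-sided 0.05; 2,000 runs per setting. r is the baseline–follow-up correlation before cut-off.

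| Mean, SD before cut-off | Zero baselines | r | Power: percent change | Power: absolute change | Power: baseline-adjusted |
|---|---|---|---|---|---|
| 3, 2 | 7% | 0.3 | 0.33 | 0.73 | 0.90 |
| 2, 2 | 17% | 0.5 | 0.47 | 0.81 | 0.93 |
| 1.5, 2.5 | 29% | 0.7 | 0.44 | 0.78 | 0.87 |

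Over all nine settings tried, power was 0.22 to 0.72 for percent change, 0.46 to 0.97 for absolute change and 0.69 to 0.99 for the baseline-adjusted analysis. Percent change was lowest each time. Patients lost per arm: 0.074 × 222 ≈ 16 up to 0.291 × 222 ≈ 65.

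**Step 4. Gain from using the baseline as a covariate, if it would otherwise not be used.** With equal variance s² at both times:

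- unadjusted change score: 2(1 − r)s²
- baseline-adjusted: (1 − r²)s²
- ratio: (1 − r²) / [2(1 − r)] = (1 + r)/2

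| r (assumed) | Ratio | Variance reduction | n per arm for 0.3 SD, 80% power: unadjusted change | n per arm: adjusted |
|---|---|---|---|---|
| 0.3 | 0.65 | 35% | 245 | 159 |
| 0.5 | 0.75 | 25% | 175 | 131 |
| 0.7 | 0.85 | 15% | 105 | 89 |

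**The case against.** The best defense is that absolute change is planned in the same sentence for the same measures. It is defined at every baseline, so pain-free patients stay in that analysis and new pain can still be seen. That stands. A reader might infer that these patients are lost to the trial's pain comparison altogether; they are lost only to one of two parallel analyses. Nor does their loss imply bias between arms: if baseline is measured before randomization, the exclusion is balanced in expectation. The cost is a changed population and lost information.

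A second temptation is to say that the plan leaves the baseline unused, or analyzes each visit separately and unadjusted. The article does not say so. Analysis by arm and by visit is compatible with a descriptive table, a repeated-measures model or a covariance analysis of change. A change score with baseline as covariate gives the same treatment estimate as the adjusted visit score. The gain in Step 4 is therefore conditional and is not evidence of an error.

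The choice of model, a main visit and the handling of deaths before later visits might be added to the complaint. A condensed article commonly leaves these to the analysis plan, which is not shown, so their absence is no finding.

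It can also be said that percent change may be meant as description only. The text does not say that; it gives both forms the same status. Finally, pain and quality of life lie outside the named test sequence, OS then PFS, and no stated success criterion depends on percent change. That stands and limits the weight of the point.

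**Conclusion.** The point holds for percent change. The article fixes it, on a par with absolute change, as an analysis variable for the BPI and EQ-5D measures, and it fails at a zero baseline, misleads at a negative index and is unstable near zero. This follows from the definition, given the instruments' score ranges. An analysis plan that follows the text inherits it.

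The size cannot be read from the article. The loss of about 16 to 65 patients per arm and the low power of percent change depend on assumed score distributions. The 15% to 35% variance reduction depends on assumed correlations of 0.7 to 0.3 and on the analysis otherwise being unadjusted, which the article leaves open.

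The consequence is modest. A sound variable is planned alongside, the endpoints are secondary, and the primary conclusion on OS is untouched. The correction is worth making because a stated analysis variable is unsuitable and replacing it is nearly free.

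**What to change.** - Delete percent change from baseline as an inferential analysis of the BPI and EQ-5D measures, or label it descriptive only and state how many patients have no value because of a zero baseline.
- Name absolute change, or the score at each visit, as the analysis variable for the between-arm comparison of cancer-related pain and quality of life.
- State that this comparison includes the baseline score as a covariate. If the unseen analysis plan already does so, a matching statement is enough.

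The covariate change concerns the two-arm comparisons only; procedure-related pain is assessed in the IRE arm alone and has no between-arm contrast. The cost is wording: baseline and follow-up scores are already collected, and no visit or sample size changes. The one downside is that there will be no inferential percent-change result.

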## Methods

### Randomized controlled trial (RCT)

The randomized, controlled, 2-arm, unblinded multicenter trial will be conducted at up to 15 sites. After subjects have been treated with 3 months of mFOLFIRINOX and there is no evidence of disease progression, they will be randomized to either a control arm or a treatment arm of IRE with the NanoKnife System using either an open or a percutaneous approach. Randomization will be conducted centrally with subjects randomized in a 1:1 ratio after assessment using a study specified imaging protocol. (Fig. 1). Post-induction treatment in the control arm and post IRE treatment for the IRE arm will be left to the discretion of the treating physician. The mFOLFIRINOX regimen will consist of oxaliplatin at 85 mg/m2, leucovorin at 400 mg/m2, irinotecan at 150 mg/m2 all on day 1, plus 5-FU at 2.4 g/m2 starting on day 1 for 46 h. This regimen will be repeated every 14 days. The minimum period of follow-up for each subject will be for 24 months or until death. Study accrual is estimated to require 36 months to complete with each subject followed until 24 months after enrollment of the last subject, or death.

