#### Sample size and statistical considerations

### Randomized controlled trial

Randomization will be conducted centrally. Concurrent randomization to either the IRE or control arm will take place at the completion of 3-month modified FOLFIRINOX administration, at participating sites, and be stratified by the response following 3 months of treatment with mFOLFIRINOX (responder vs. stable disease), planned type of IRE procedure (open or percutaneous) and planned post-procedure treatment (chemotherapy versus radiotherapy/ chemotherapy versus observation). A total of 444 Intent-to-treat population (ITT) subjects (with 222 subjects in each arm) are required for at least 80% power for the primary efficacy endpoint (OS), with the expectation that there will be a total of 380 events in both arms. With the consideration of up to 16% attrition rate in both arms, and assuming a median survival of 12 months and exponential survival, up to 528 subjects (with 264 subjects per arm) will need to be randomized.

The sample size consideration for the primary endpoint OS was based on the assumptions that 1) there will be a 1:1 randomization scheme, 2) median survival will be 12 months and 16 months in the control and the IRE arm, respectively, i.e., a hazard ratio of 0.75 for IRE versus control 3) there will be a 5% 2-sided type I error, 4) there will be an accrual period of 36 months and follow-up period of 24 months after the study is fully enrolled. In addition, based on an assumption that median times to PFS will be 6 months and 8 months in the control and IRE arm, respectively, the study has at least 80% power for analysis of the difference in the secondary endpoint of time to PFS between the IRE and control arms.

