For the secondary efficacy analysis, the null hypothesis for PFS is H_0_: μ_control_ = μ_IRE_ with the alternative hypothesis being H_1_: μ_control_ ≠ μ_IRE_,where μ_control_ is the median PFS time for the control arm, and μ_IRE_ is the median PFS time for the IRE arm. This study is powered to show the superiority of PFS of 2 months in the IRE arm over the control arm. The above null hypothesis will be tested by a 2-sided log rank test at 0.05 significance level only if the result of testing the primary efficacy endpoint is statistically significant. If the above null hypothesis is rejected by the two-sided test and the observed median PFS time in the IRE is greater than in the control arm, the alternative hypothesis will be established and the superiority of the PFS in the IRE arm will be statistically proven.

Analysis of the primary efficacy endpoint and key secondary endpoints will also be performed for the mITT population as supportive analyses. Safety analysis will be performed on the Safety population. To control the overall type I error rate for testing efficacy endpoints, a fixed-sequence testing procedure will be used to test the primary and secondary efficacy endpoints in a predefined order. The test will be performed in sequence and significance of OS endpoint is required in order to proceed to the testing of PFS endpoint. All statistical tests will be at the two-sided 0.05 significance level and the corresponding *p*-values and 95% confidence intervals (CIs) will be reported. Subjects alive or lost to follow-up at the time of analysis will be censored at their last date of follow-up. In the final analysis, OS will be compared between the randomized treatment arms using a two-sided log-rank test at a type I error rate of 0.05. ITT analysis will be the primary analytic methods, supported with mITT and Cox proportional hazards analysis. Kaplan-Meier methods will be used to summarize survival distribution of OS and median OS time for each treatment arm. The relative treatment effect between the IRE arm and the control arm with respect to OS will be estimated by the hazard ratio (HR) and the associated two-sided 95% CIs using the Cox proportional hazards model.

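### The only formally tested safety endpoint counts all deaths, so an overall survival gain of the planned size can offset a rise in Grade 4 adverse events

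*Protocol article*

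**What the plan says.** Assessing the safety of IRE against control is a primary objective (Protocol article, Study objectives). The endpoint section gives two co-primary safety endpoints. The first is worded "Co-primary safety endpoints include time (in months) from randomization or enrollment in the registry to death or new onset of Grade 4 AE". The second is any adverse event of Grade 3 or higher.

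Statistical analysis, Randomized controlled trial, treats the two differently:

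- For the first, the method is a log-rank test to "compare the time (in months) from randomization to death or new onset of Grade 4 AEs for the two treatment arms". The same section states "All statistical tests will be at the two-sided 0.05 significance level". It gives no margin and no hypothesis of harm for safety.
- For the second, the output is the "number and proportion of subjects with a high-grade complication defined as any AEs or SAEs with a CTCAEv5.0 grade of 3 or higher". The article says only that this "will be summarized by treatment arm and CTCAE grade". No test is attached to it.

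The composite is therefore the only co-primary safety endpoint with a formal test. Death from any cause is also the primary efficacy event. The planning assumption for that event is that "median survival will be 12 months and 16 months in the control and the IRE arm, respectively, i.e., a hazard ratio of 0.75", and the interim-analysis text says that the study is powered on overall survival. Follow-up is long: "each subject followed until 24 months after enrollment of the last subject, or death".

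**The concern.** A composite of death and Grade 4 events responds to the sum of two hazards. In this population the death hazard is likely to be the larger, and the trial is designed to show that IRE lowers it. An added Grade 4 hazard under IRE then pulls the composite one way while the hoped-for survival gain pulls it the other. The better the device works on survival, the less the safety test can say about toxicity.

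What is at stake is the safety conclusion. A non-significant composite, or one that leans towards IRE, would be compatible with a real and sizeable increase in Grade 4 events.

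**Working it through.** **1. The plan's own figures.** At hazard ratio 0.75, two-sided 0.05 and 80% power, the deaths needed are 4 × (1.96 + 0.8416)² / (ln 0.75)² = 379.4, that is 380 as stated. With exponential survival, uniform accrual over 36 months and 24 months of further follow-up, the proportion with an event at total hazard s is

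f(s) = 1 − [exp(−24s) − exp(−60s)] / (36s).

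For 222 subjects per arm this gives about 381 deaths, in line with the stated 444 subjects and 380 events.

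**2. Death hazards.** Control: ln 2 / 12 = 0.0578 per month. IRE: ln 2 / 16 = 0.0433 per month. The difference, 0.0144 per month, is the added Grade 4 hazard at which the composite hazard ratio equals 1.0 under constant hazards, whatever the control Grade 4 rate. For a doubling, the break-even control rate is therefore 0.0144 per month, a 12-month risk of 1 − exp(−12 × 0.0144) = 16%.

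**3. Composite against Grade 4 alone, 444 subjects.** The article gives no Grade 4 rate for either arm, so the control Grade 4 hazard h is an assumption: 0.01 or 0.02 per month (12-month risk 11% or 21%). With multiplier m under IRE:

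- Composite hazard ratio = (0.0433 + m·h) / (0.0578 + h).
- Composite events = 222 × [f(control) + f(IRE)], with s the total hazard in each arm.
- Grade 4 first events = the same sum, each term multiplied by (Grade 4 hazard / total hazard).
- Power to show harm = Φ(√(events/4) × ln HR − 1.96).

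| h, m | Composite HR | Composite events | Power, composite | Grade 4 first events | Power, Grade 4 alone |
|---|---|---|---|---|---|
| 0.02, 1.5 | 0.0733/0.0778 = 0.94 | 419 | under 1% | 139 | 67% |
| 0.02, 2 | 0.0833/0.0778 = 1.07 | 423 | 11% | 156 | 99% |
| 0.01, 2 | 0.0633/0.0678 = 0.93 | 408 | under 1% | 94 | 92% |

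For the second row: √(423/4) × ln 1.0715 − 1.96 = −1.25, and Φ(−1.25) = 0.11. For Grade 4 alone: √(156/4) × ln 2 − 1.96 = 2.37, and Φ(2.37) = 0.99.

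**4. Simulation, 264 per arm, Grade 4 risk doubled.** Two-sided 0.05 log-rank tests, 4000 runs, control median survival 12 months. Ranges span a constant Grade 4 hazard (risks at 12 months) and Grade 4 events clustered in the first 3 months. The control risks are assumed. The upper two, once doubled, equal the 21% and 34% that the Background section reports for Grade 3 or higher complications after IRE. Those are not Grade 4 rates and serve only to set a range.

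| Grade 4 risk, control vs IRE | Composite shows harm, OS HR 0.75 | Composite favours IRE, OS HR 0.75 | Composite shows harm, OS HR 0.90 | Composite shows harm, OS HR 1.0 | Grade 4 alone shows harm, OS HR 0.75 |
|---|---|---|---|---|---|
| 5% vs 10% | 0% | 46–60% | 1% | 9–12% | 56–72% |
| 10.5% vs 21% | 0.1–0.5% | 10–24% | 5–12% | 25–36% | 90–96% |
| 17% vs 34% | 2–10% | 0.4–3% | 28–46% | 58–74% | 99% or more |

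At 30% vs 60%, the composite shows harm in 79–94% of runs even at OS hazard ratio 0.75.

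**The case against.** There is a sound reason to include death: it captures fatal toxicity without a judgement on cause and avoids treating death as ordinary censoring. That supports keeping the composite. It does not make the composite informative about Grade 4 events.

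Four stronger readings are tempting, and the article does not support them.

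- *The endpoint cannot see a doubling of Grade 4 events.* This depends on an unstated control rate and on the survival gain. With no survival gain, a doubling from 0.02 per month gives a composite hazard ratio of (0.0578 + 0.04) / (0.0578 + 0.02) = 1.26, with about 66% power at 444 subjects and 73% at 528. At about 30% control risk the masking ends even with the planned gain.
- *The harm would be hidden from all output.* The Grade 3 or higher endpoint is summarized by arm and by grade. In the doubling from 0.02 per month, about 24% of control and 46% of IRE subjects would have a first Grade 4 event, and that gap would be plain in the table. It is hidden from the formal test only.
- *The plan treats non-significance as proof of safety.* No such rule is stated. Decision rules are given for overall and progression-free survival, none for safety. There are also device-specific stopping rules and data monitoring committee oversight, although these are not endpoints and do not estimate the general Grade 4 excess.
- *The Grade 3 or higher proportion is defective because no time window is given.* A condensed article may leave this to the full protocol, so it is not part of this point.

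What stands is narrower. The composite and its test are stated design choices, not omitted detail, and at the trial's own planning values they say little about Grade 4 toxicity.

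**Conclusion.** The concern holds in limited form. The one formally tested co-primary safety endpoint contains the primary efficacy event and tests only for a difference. At the planned survival hazard ratio of 0.75 it absorbs about 0.014 extra Grade 4 events per person-month before it turns against IRE. For assumed control rates of 0.01 and 0.02 per month, its power to show a doubling is under 1% and about 11%, against about 92% and 99% for Grade 4 events alone. At low control rates it may even be significant in favour of IRE.

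These sizes rest on assumed Grade 4 rates, on exponential death times and on a survival gain near the planned one. They shrink as the survival gain shrinks. With no gain at all, deaths still dilute the comparison, but they no longer offset the harm. The consequence is for what the trial can conclude on its safety objective; the efficacy analysis is not affected.

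**What to change.** Keep the composite as a co-primary endpoint. Demoting it would change endpoints fixed in a trial approved under an investigational device exemption, and the repair does not need that.

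Add one pre-specified key safety analysis: time from randomization to first new Grade 4 adverse event, with death without a prior Grade 4 event as a competing event. Report cumulative incidence by arm and the cause-specific hazard ratio with its 95% confidence interval. Both are needed, because longer survival by itself raises cumulative incidence. State that the conclusion on Grade 4 toxicity rests on this estimate and its interval, and that a non-significant composite log-rank test will not be taken as evidence that toxicity is similar.

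The data are already collected for the composite and the output is standard. The cost is one more safety analysis to specify and report, and a possibly less favourable safety picture.
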